## **7. Intervention**

### *7a. Algorithm data collection*

The SLATE algorithm (illustrated in Figure 1 above) calls for four types of screens: a symptom report, medical history, brief physical exam, and readiness assessment. Each of these is described below and further detail is provided in the case report form appended to this protocol. A negative response to a screen indicates that the patient “screens out” and referral for additional care (consultation, laboratory test, counselling, other) is recommended; if all responses are positive, then the patient “screens” in for immediate initiation under SLATE.

1. Symptom report. Each patient will be screened for current cough, fever, night sweats, and weight loss, which comprise the standard, WHO-recommended TB symptom screen, and for persistent (continuous) headache for more two days, which is a symptom of cryptococcal meningitis, and will be asked about any other symptoms that the patient has noticed.
2. Medical history: To identify individuals who are likely to face problems with medication-taking or adherence, patients will be asked if they have ever been on ART previously, started TB treatment in the past two weeks, are taking concurrent medications for epilepsy or warfarin, which can interact with ARVs, or have a history of substance abuse.
3. Physical exam: A brief, symptom-guided physical exam to look for causes of symptoms or any other evident conditions that could postpone ART initiation will be conducted.
4. Readiness assessment and counselling: A published review of readiness instruments for HIV initiation found that none was notably successful in predicting patient readiness for ART, as indicated by adherence once on treatment. Despite this, there is general consensus that explicit attention to readiness is an important component of treatment initiation. Drawing on the published literature on stage-of-readiness scales, we have created a short instrument which we expect to serve primarily as an invitation to patients to raise concerns or questions about treatment readiness with the clinician conducting the assessment. Following the questions, the study clinician will have a brief conversation with the patient to confirm that the patient feels ready to start treatment immediately, understands what happens next, and has no further questions or concerns.

If SLATE were used in routine care, we expect that the screens would be administered sequentially, so that a negative response on the first screen would cause a patient to screen out without having to complete the second screen, and so on. Patients would progress to the next screen only after being found positive on the previous one. For purposes of this study, however, we will administer all four screens, to obtain a complete algorithm data set for each patient in the intervention arm.

We anticipate that for the vast majority of patients, the first three screens will take less than 5 minutes each to administer and the last screen less than 10 minutes. Patients who screen out will require more time, and we therefore estimate needing an average of up to 30 minutes of clinician time per patient in the intervention arm.

### *7b. Blood draw*

Cryptococcal meningitis and other co-infections are more likely in patients with very low CD4 counts. Although new national guidelines in the study countries do not require the results of a CD4 count to establish treatment eligibility, most countries will continue to use CD4 counts to monitor patient condition. To avoid asking intervention group patients to wait in the clinic's queue for a blood draw, the study clinician will do a standard venous blood draw, following the same procedures that the clinic would otherwise use. Blood samples will be tested by the laboratories that serve the clinics, following routine procedures, and results will be placed in routine medical records so that the study clinics do not have to repeat the CD4 count for the same patients. The clinic may also use the blood sample for other baseline tests recommended in national guidelines, such as creatinine, hemoglobin, and for patients with CD4 counts under 100 cells/mm^3, cryptococcal antigen (CrAg). The clinic will follow routine procedures for laboratory tests; the study will only be responsible for drawing the required blood sample.

Study staff will monitor CD4 count results for all patients enrolled in the intervention arm. Under national guidelines in both countries, any patient who has a CD4 count under 100 cells/mm^3 and a positive cryptococcal antigen (CrAg) screening result should begin presumptive treatment for cryptococcal meningitis. Results of the CD4 count and CrAg screening test will only be available several days after study enrollment, however. To facilitate proper follow up of any intervention arm patient who does have a positive CrAg screening test, study staff will review CD4 count results for intervention arm patients as soon as the results are available at the study clinics. The study team will alert the clinic to any patient who has a CD4 count under 100 and request that the clinic trace the patient and provide follow up care as guidelines mandate.

### *7c. Referral of patients who screen out*

After completing all four of the SLATE screens, the study clinician will fill out a brief referral letter that reports any substantive findings, such as TB symptoms or a physical exam observation. Intervention arm patients who screen out (have negative responses on any of the SLATE screens) will be referred to routine clinic care to address the issue(s) identified and initiate ART under standard care. The study clinician will discuss and explain the concern(s) with the patient and then escort the patient to the registration desk to continue with a standard clinic visit. The patient will be given the referral letter and encouraged to give the letter to the clinic nurse or medical officer. Patients who do not wish study findings to be shared with clinic staff will not be required to pass on the letter. Patients who are referred to routine care due to a positive SLATE screen will remain in the intervention arm, have the same study follow up as other intervention arm participants, and be analyzed as part of the intervention arm.

For patients who screen in (have positive responses on all the SLATE screens and are eligible for immediate ART initiation) give their agreement, referral letters will be placed in their clinic files along with other source documentation, such as the regular ART record that must be filled out for all new ART patients. Letters will not be filed for patients who do not agree.

### *7d. Dispensing of ARVs and prophylaxis*

Patients who have a full negative SLATE screen (no reasons for delay) will immediately be offered their first supply of ARV medications. While making the offer to dispense, the study clinician will confirm that

the patient still wishes to start ART immediately, answer any questions the patient may have, and reiterate the importance of returning for the patient's next appointment and medication refill.

In addition to ARVs, national guidelines call for prescribing isoniazid preventive therapy (IPT) and/or co-trimoxazole prophylaxis to new HIV patients. The study clinician will also write prescriptions for these medications. Where possible, the study clinician will have a stock of medications in the study room, so that the patient does not need to go anywhere else in the clinic to obtain their medications. If this is not allowed, the study clinician or study assistant will escort the patient to the clinic pharmacy to obtain the medications without waiting in a queue. The clinician or study assistant will then escort the patient to the clinic registration desk to schedule the next appointment, which will include participation in one of the clinic's routine adherence education sessions.

#### *7e. Completion of direct study interaction and payment*

Direct study interaction with study subjects will cease as follows:

- *Intervention group (Track 1)*: Upon completion of the ART initiation steps described above, after which subjects will be managed by the study site following standard procedures.
- *Standard group (Track 1)*: after randomization, at which point subjects will be managed by the study site following standard procedures.

From these points on, all subjects, regardless of which type of initiation they received, will be managed by the site following its routine procedures for pre-ART and ART care. Because this study evaluates routine practice and uses retention in care as an outcome, any further study interaction with subjects would affect the results, in particular loss to follow-up. There will therefore be no post-baseline study visits, only routine care visits not involving study personnel. Standard procedures will also be implemented by the study site (not the study team) for study subjects who miss scheduled visits.

The last step in study interaction for both groups will be payment. Reimbursement to consented study subjects of the equivalent of \$5-\$15 will be provided as a token of appreciation for study participation. The exact amount will be determined in consultation with the study sites and local study teams. The reimbursement will be in the form of cash in Kenya and a voucher to a nearby supermarket and general goods store in South Africa.

### **8. Medical Record Follow Up**

Study subjects in both arms will be followed passively through review of routine medical records kept by the study sites for up to 14 months after study enrollment. This will capture up to 1 month for treatment initiation, up to 12 months of follow up, and up to 1 month for a 12-month routine visit to be made.

The purpose of medical record follow up is to determine which patients enrolled in the study did go on to initiate ART and after what time interval, their early outcomes on treatment, and resource utilization (cost) of initiating ART.

Specific data fields to be collected from medical records are listed under Data Collection below.

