##### *4b. Secondary objectives*

The secondary objectives of this study are to:

3. Compare the proportion of study-eligible patients who initiate ART within 14 days of study enrollment between HIV-infected patients offered immediate ART initiation under the SLATE algorithm and patients offered standard ART initiation.
4. At sites where viral load data are available, compare the proportion of study-eligible patients who initiate ART and are virally suppressed eight months after having an HIV test or enrolling in HIV care
5. Compare the proportion of study-eligible patients who initiate ART and are alive, in care, and retained on ART by 14 months and 16 months after study enrollment between HIV-infected patients

offered immediate ART initiation under the SLATE algorithm and patients offered standard ART initiation.

6. Estimate the proportion of HIV-positive patients presenting at study clinics and not yet on ART who are eligible or ineligible for immediate initiation using SLATE algorithm criteria.
7. Describe reasons for ineligibility for immediate initiation, among those found ineligible in the intervention arm.
8. Estimate average time interval in days between study enrollment and ART initiation for each study arm.
9. Describe self-reported patient preferences on the speed and timing of ART initiation.
10. Estimate costs to patients of implementing the SLATE algorithm, compared to standard care.
11. Estimate costs to providers of implementing the SLATE algorithm, compared to standard care.

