#### *Exclusion criteria:*

- Pregnant (pregnancy is an exclusion criterion because treatment guidelines for pregnant women differ from those for non-pregnant adults; most pregnant women are diagnosed with HIV and initiated on ART in antenatal clinics, not general adult HIV clinics)
- Not intending to return to this clinic for further HIV care in the coming year (i.e. intends to seek further care somewhere else)
- Not physically, mentally, or emotionally able to participate in the study, in the opinion of the investigators or study staff
- Not willing or able to provide written informed consent to participate in the study
- Previously enrolled in the same study

All the study countries have adopted a policy of “treat all” or “test and treat”, so that all SLATE study subjects will also be eligible for ART under national guidelines. Although implementation of this policy may not be complete and may vary by site, we will enroll all patients who would be eligible under expected treat all guidelines regardless of actual clinic-specific practice at the time of the study. This will

ensure that the SLATE study can generate information for a future in which “treat all” is the standard in most places.

Patients will be followed passively through medical record review for up to 16 months after study enrollment.

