#### *9e. Medical record data*

Once the CRF has been completed, all remaining patient-level data for the study will be collected from routinely maintained medical records. The format of these records will vary by study country and site. Some sites will use electronic medical records, while others will rely on paper-based records and registers or a combination of electronic and paper. We will access all available records for each study

patient, regardless of format or storage location, to try to obtain as complete a study data set as possible. The fields we will aim to capture are listed below.

*To be used to link electronic and paper-based records to study identification number only:*

- Electronic medical record system number
- Clinic file numbers
- National ID number
- Name
- Date of birth
- Sex

*All subjects at clinic visit on date of study enrollment:*

- Date of positive HIV test (if available)
- CD4 count (most recent)
- Date and result of TB symptom screen, if done
- Date, type, and result of TB test(s) (current and previous, if any)
- TB treatment, if offered (date of initiation)
- WHO stage and clinical conditions

*Subjects who are eligible for ART initiation at the study clinic:*

- Reasons for delaying ART initiation, if relevant
- Date ART initiated (first dose of drugs dispensed)
- First-line regimen prescribed

*For all clinic visits for duration of study follow up, from study enrollment to the follow-up endpoints indicated above:*

- Date of visit
- Primary reason for visit (e.g. pre-ART visit, scheduled medical visit, medication pickup, unscheduled medical visit)
- Types of professionals seen (e.g. nurse, doctor, pharmacy assistant, counselor)
- Group and individual sessions attended (e.g. wellness course, adherence education)
- Numbers and types of all lab tests conducted (including CD4 counts, viral loads, CrAg test, blood tests to determine ARV regimen)
- Other procedures (e.g. x-rays) performed
- Medications prescribed and dispensed (ARV and non-ARV, including isoniazid and cotrimoxazole)
- Admissions for inpatient care since previous visit, if recorded
- Details of inpatient care received (facility, number of days, medications, lab tests, etc.) if recorded

*At follow-up endpoints (6 and 12 months after ART initiation or comparable timepoint for those who do not initiate ART):*

- Date and result of most recent viral load test

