- Status at clinic (in care / died / transferred to another site / stopped care / lost to follow up, defined as > 1 month late for last medication pickup)
- New or recurring HIV-related conditions
- Date and cause of death if applicable
- Date and result of most recent CD4 count

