## **12. Outcomes and Data Analysis**

### *12a. Outcomes*

The primary outcomes for the study are:

1. The proportion of patients initiated on ART within 28 days of study enrollment. While national guidelines recommend ART initiation within two weeks of a patient's first clinic visit or HIV diagnosis, recent studies suggest that 28 days is a more realistic deadline for routine care.

2. The proportion of patients who initiate ART and are alive, in care, and retained on ART eight months after study enrollment. Eight months was selected to allow up to 1 month (28 days) to initiate ART, six months of follow up after treatment initiation, and up to 1 month to return for the six-month routine clinic visit.

These outcomes were proposed in a paper published by the investigators based on the MATI technical consultation described in protocol section 3c.

Secondary outcomes will include:

3. The proportion of patients initiated on ART within 14 days of having an HIV test or enrolling in HIV care.
4. The proportion of patients who initiate ART and are virally suppressed eight months of having an HIV test or enrolling in HIV care between HIV-infected patients offered immediate ART initiation under the SLATE algorithm and patients offered standard ART initiation.
5. The proportions of patients who initiate ART and are alive, in care, and retained on ART 14 and 16 months after having an HIV test or enrolling in HIV care. Fourteen months extends the primary outcome endpoint, which is at 8 months, by an additional six months. Sixteen months allows loss to follow up at 12 months to be defined as three months late for the 12-month visit, which is a common endpoint in the literature (16 = 1 month to initiate ART + 12 months' follow up + 3 months to attend 12-month visit).
6. The proportions of HIV-positive patients presenting at study clinics and not yet on ART who are eligible and ineligible for immediate initiation using SLATE algorithm criteria.
7. Reasons for ineligibility for immediate initiation, among those found ineligible in the intervention arm.
8. Average time to ART initiation (days) for each arm.
9. Patient preferences on the speed and timing of ART initiation.
10. Costs to patients of ART initiation under standard and intervention procedures.
11. Costs to providers of ART initiation under standard and intervention procedures.

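### Record review ends at 14 months in section 8 but at 16 in section 5c and outcome 5, and section 9e dates status and viral load from ART initiation, not from the outcome time points

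*Protocol*

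**What the plan says.** **Length of follow-up.** Section 8 states that subjects in both arms are "followed passively through review of routine medical records kept by the study sites for up to 14 months after study enrollment" and gives a reason: "This will capture up to 1 month for treatment initiation, up to 12 months of follow up, and up to 1 month" for the 12-month visit to take place. The end of section 5c states: "Patients will be followed passively through medical record review for up to 16 months after study enrollment". Secondary objective 5 (section 4b) compares the proportions "retained on ART by 14 months and 16 months after study enrollment between HIV-infected patients" in the two arms. Section 12a explains the later time point: "Sixteen months allows loss to follow up at 12 months to be defined as three months late for the 12-month visit".

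**Timing of status.** Primary outcome 2 (section 12a) is the proportion who start ART and are alive and "retained on ART eight months after study enrollment". Outcome 4 is viral suppression at eight months, and outcome 5 is retention at 14 and 16 months. The endpoint fields in section 9e (clinic status, death, latest viral load and CD4 results) are dated "6 and 12 months after ART initiation or comparable timepoint for those who do not initiate ART". The status codes include "lost to follow up, defined as > 1 month late for last medication pickup".

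**What else is abstracted.** Section 9e also lists, for every clinic visit during follow-up, the visit date, the medications dispensed, and the number and types of laboratory tests.

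**The concern.** Section 8 is where an abstraction team would look for the stopping point. The 14 and 16 month figures each carry their own rationale, so neither can be dismissed as a typing error. A team that stops at 14 months loses a stated secondary outcome, and an analysis plan cannot recover records that were never abstracted.

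The second problem is one of clocks. The outcomes do not run from ART initiation, but the endpoint fields do. The intervention is meant to bring initiation forward, so a field dated from initiation falls at a different point after enrollment depending on how quickly a patient starts. If the abstraction form is built from section 9e as written, no status field and no viral load result is tied to month 8, 14 or 16.

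**Working it through.** **Follow-up windows.** The protocol's own sums reproduce:

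- Section 8: 1 + 12 + 1 = 14 months.
- Section 12a, 16-month outcome: 1 + 12 + 3 = 16 months.
- Section 12a, primary outcome 2: 1 + 6 + 1 = 8 months.

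Section 8 therefore stops 16 − 14 = 2 months before the last outcome time point, while section 5c matches it. Early starters do not close the gap. A patient who starts on day 0 has a 12-month visit due at month 12 and is three months late only at month 12 + 3 = 15, which is also after month 14.

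**Where the section 9e fields fall after enrollment.** Month of field = (days to initiation ÷ 30.44) + 6 or + 12.

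| ART start | 6-month field | Short of month 8 | 12-month field | Short of month 14 | Short of month 16 |
|---|---|---|---|---|---|
| Day 0 | 6.0 | 2.0 | 12.0 | 2.0 | 4.0 |
| Day 14 | 6.5 | 1.5 | 12.5 | 1.5 | 3.5 |
| Day 28 | 6.9 | 1.1 | 12.9 | 1.1 | 3.1 |

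Among patients who start within 28 days, the field varies by at most 28 ÷ 30.44 = 0.92 month. A patient who starts after about 2 × 30.44 = 61 days has the 6-month field after month 8.

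If the field is read generously, with a further month to establish that a pickup is more than one month late, it falls at month 7.0 (day 0) to 7.9 (day 28). That is still before month 8.

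**What can be rebuilt from visit-level data.**

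- *Retention at month 8:* yes. Visit and dispensing dates are listed for every visit, and even the 14-month window covers month 8.
- *Death:* yes, because its date is listed.
- *Transfer or stopping care:* only in part. Both are status codes with no date listed.
- *Viral load result:* no. The visit-level list covers the number and types of tests, and results appear only in the endpoint fields. A day-0 starter whose six-month test is done in the extra month that section 12a allows (months 6 to 7) can have a result after the 6-month field. It would then be captured only at the 12-month field, and only if no later test had replaced it as the most recent.
- *Retention at month 16:* only if abstraction continues to month 16, which is where sections 5c and 8 disagree.

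Section 12a counts outcomes 4 and 5 from the HIV test or entry to HIV care, while section 4b counts objective 5 from study enrollment. Neither is ART initiation, so the mismatch with section 9e holds under either.

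**The case against.** The strongest reply is that the needed data are mostly planned. Section 5c provides for 16 months of record review. Section 9e abstracts visits and dispensing throughout follow-up, section 9g has paper files pulled periodically, and section 12b already extracts resource use at 8 months after enrollment. Nothing says that the status field is the endpoint. This stands for primary outcome 2: month-8 retention can be derived on the enrollment clock in both arms. It does not settle the 14 versus 16 month conflict, and it does not supply viral load results.

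A reader might infer more than the documents support:

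- **That months 14 to 16 will be unobserved for every patient.** This follows only if section 8 prevails. Section 5c plans otherwise.
- **That losses before month 8 are missed mainly in the intervention arm, favouring the intervention on primary outcome 2.** This requires the status field to be used as the endpoint. The shortfall is also not confined to one arm: standard-arm patients who start within 28 days have the field at months 6.0 to 6.9 too, and intervention patients who screen out start under standard care. The protocol gives no monthly attrition rate, so no bias in percentage points can be derived from it.
- **That the one-month and three-month lateness rules contradict each other.** Section 12a adds month 16 precisely to allow the three-month rule. The one-month rule fits the 8-month and 14-month windows.
- **That the vague time point for non-initiators distorts primary outcome 2.** That outcome requires ART initiation, so non-initiators fail it whenever their status is recorded.

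**Conclusion.** The point holds as two inconsistencies that should be fixed. First, section 8 contradicts section 5c and outcome 5 by two months; followed literally, it makes the 16-month retention outcome impossible to determine. This rests on the text alone. Second, the endpoint fields in section 9e are on a different clock from the outcomes. For patients who start within 28 days they fall 1.1 to 2.0 months before months 8 and 14, and 3.1 to 4.0 months before month 16.

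For primary outcome 2 this is a recoverable ambiguity, not a demonstrated bias, provided retention is derived from visit and dispensing dates. The 8-month suppression outcome is more exposed, because results are listed only at the initiation-dated fields. That conclusion assumes the abstraction form follows the list in section 9e; electronic downloads may hold more, but the protocol does not say so.

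**What to change.** 1. **Section 8:** change 14 to 16 months and replace the 1 + 12 + 1 rationale with 1 + 12 + 3, to match section 5c and outcome 5.
2. **Section 9e:** replace the initiation-dated time points with 8, 14 and 16 months after study enrollment, identical in both arms and applied whether or not ART was started. At each, record clinic status (with the date of any transfer or stopping of care), last visit, last dispensing, death, and latest viral load result with its date.
3. **Derivation:** state that retention is derived from visit and dispensing dates, with the three-month lateness definition applied at 16 months as section 12a describes.
4. **Section 12a and objective 4:** while amending, state study enrollment as the starting point for outcomes 4 and 5, so that the fields and the outcomes share one clock.

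The cost is a wording amendment and a small change to the abstraction form, with no patient contact and no follow-up beyond what section 5c already plans. It should be done before abstraction at the affected time points.
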